# Efficacy and safety of Shu-gan-qing-re formula for generalized anxiety disorder: study protocol for a multi-center, prospective, double-blind, double-dummy, randomized controlled trial

**DOI:** 10.1186/s13063-020-4186-6

**Published:** 2020-03-14

**Keywords:** Generalized anxiety disorder (GAD), Shu-gan-qing-re (SGQR) formula, Traditional Chinese medicine (TCM)

## Abstract

**Background:**

Generalized anxiety disorder (GAD) is a persistent and common mental disorder that entails significant impairments in role functioning and quality of life. Currently available effective interventions include psychological therapies, self-help approaches, and pharmacological treatments, which do not quite meet clinical needs, and the ideal anxiolytic is still being sought. Shu-gan-qing-re (SGQR) formula, a Chinese patent medicine, has been well received by patients with GAD in Chinese clinical practice for years. The present prospective, double-blind, double-dummy, randomized controlled trial is designed to investigate the efficacy and safety of SGQR formula for GAD.

**Methods/design:**

A total of 200 eligible participants will be recruited from four hospitals in different parts of China. They will be randomly assigned to either the study group or the control group in a ratio of 1:1. Participants allocated to the study group will receive SGQR formula and buspirone placebo, while buspirone and SGQR placebo will be applied in the control group. Six scheduled visits will be conducted over the course of 8 weeks. Outcome measurements include Hamilton Anxiety Rating Scale (HAM-A), Hamilton Depression Rating Scale-17 (HAMD-17), Clinical Global Impression-Improvement Scale (CGI-I), Traditional Chinese Medicine Syndrome Scale for GAD, and pro-inflammatory cytokine tests: interleukin-1 beta (IL-1β), IL-6, and tumor necrosis factor-alpha. Adverse reactions will be evaluated by using the Treatment Emergent Symptom Scale (TESS). Safety outcomes and adverse events will also be recorded.

**Discussion:**

The study will provide scientific and objective assessments for the efficacy and safety of SGQR formula for patients with GAD, hopefully offering clinicians an alternative approach to GAD.

**Trial registration:**

Chinese Clinical Trial Registry, ID: ChiCTR-IPR-17013058. Registered on October 20, 2017.

## Background

Generalized anxiety disorder (GAD) is a persistent and common disorder characterized by feelings of threat, restlessness, irritability, sleep disturbance, tension, and symptoms such as palpitations, dry mouth, and sweating [1]. An epidemiological study in China suggested that the illness has a lifetime prevalence of 0.3% and a 12-month prevalence of 0.2% (the highest prevalence is in the 50- to 64-year-old group) but shows no gender difference [2]. The high prevalence of concurrent psychiatric disorders makes the diagnosis of GAD difficult, possibly contributing to the different epidemiological results of China, Europe, and the US [3, 4]. Comorbidity with at least one other mental disorder at some point troubles the majority of patients with GAD, most commonly with major depressive disorder [1, 5]. Besides, GAD is associated with considerable economic costs owing to work productivity loss and high medical resource use. The role impairments of pure GAD are similar in magnitude to those of major depressive disorder [5].

GAD has a relapsing course, and treatments rarely result in complete resolution of symptoms. In the short to medium term, effective intervention includes psychological therapies, such as cognitive behavioral therapy; self-help approaches based on cognitive behavioral therapy principles; and pharmacological treatments [1]. Until the mid-1980s, pharmacological treatment options consisted primarily of benzodiazepines, which later became an effective short-term therapy in consideration of their abuse potential. For patients requiring long-term treatment, buspirone and some newer antidepressants became the alternatives. Nevertheless, the mild efficacy combined with a slow onset of action dampened the satisfaction with buspirone, whereas antidepressants, mainly selective serotonin reuptake inhibitors (including paroxetine), brought both efficacy and lots of adverse effects [6]. The search for the ideal anxiolytic has never stopped.

Traditional Chinese medicine (TCM) is the most popular alternative and complementary medicine in China. It has a long history in the treatment of mental disorders and has favorable clinical effectiveness. According to the theory of TCM, anxiety results mainly from the stagnation of the liver qi, and inner heat emerges as a result. Shu-gan-qing-re (SGQR) formula is tailored from famous TCM prescriptions: Xiao-yao powder and Gan-mai-da-zao decoction. It is composed of Radix Paeoniae Alba, Radix Bupleuri, Angelica Sinensis, and seven other herbals and functions by smoothing the liver qi. SGQR formula can help to relieve anxiety and has been used in Chinese clinical practice for years.

The present multi-center, prospective, double-blind, double-dummy, randomized controlled trial is designed to investigate the efficacy and safety of SGQR formula, setting buspirone as the control treatment. We hope that, through this rigorously designed study, we can provide scientific and objective assessments for the efficacy and safety of SGQR formula for patients with GAD and possibly offer the world an alternative anxiolytic.

## Methods/design

### Study design

This is a multi-center, prospective, double-blind, double-dummy, randomized controlled trial. The flowchart of the study is presented in Fig. 1.

**Fig. 1 Fig1:**
[figure not shown]
Study design

### Ethical issues

The clinical trial has been registered on the Chinese Clinical Trial Registry (ChiCTR-IPR-17013058). The study protocol (version 2.0 in August 2017) has been approved by the research ethics committee of Beijing Anding Hospital, Capital Medical University ((2017)63-201772FS-2). The research ethics committee will also be responsible for supervising all procedures of the study, including participant recruitment, randomization, conduction, and data storage. In case of any changes to the study protocol, we will submit a written application to the research ethics committee. They will decide whether it is acceptable to make the change.

### Participant recruitment

A total of 200 eligible participants will be recruited from four hospitals in different parts of China: Beijing Anding Hospital, Xiamen Xianyue Hospital, Tangshan 5th Hospital, and Zhumadian 2nd People’s Hospital. Both inpatients and outpatients will be screened for participation from November 2017.

### Informed consent

Potentially eligible patients will be invited to take part in our study. Prior to enrollment, researchers will fully introduce the detailed procedures of the study to the patients. All questions and concerns raised about the study will be addressed at length. Patients will also be informed of the probable benefits and potential risks and assured that participation is entirely voluntary. Patients who meet all of the inclusion criteria and none of the exclusion criteria will be enrolled after providing written informed consent. The personal information of all the participants will always be kept confidential.

### Criteria

#### Inclusion criteria

Participants meeting all of the following criteria will be enrolled: (1) inpatients or outpatients with GAD diagnosed in accordance with the International Classification of Disease-10; (2) those with a diagnosed TCM pattern of liver-qi stagnation transforming into fire, which usually manifests as irritability, constriction in the chest, hypochondriac distention, gastric discomfort with acid regurgitation, dry mouth or bitter taste in the mouth (or both), constipation, headache, conjunctival congestion, tinnitus, reddened tongue with yellow fur, and rapid pulse; (3) ages between 18 and 65 (no limitation on gender); (4) Hamilton Anxiety Rating Scale (HAM-A) scores between 14 and 39 (inclusive) at screening and baseline; and (5) written informed consent obtained either personally or by proxy.

#### Exclusion criteria

Participants meeting any one of the exclusive criteria will not be enrolled: (1) patients with serious suicidal tendencies; (2) patients with glaucoma; with severe or unstable internal medical conditions involving mainly the heart, liver, kidney, endocrine system, or the blood; or with diseases that may induce acute or chronic abnormal levels of pro-inflammatory cytokines (systemic lupus erythematosus, ulcerative colitis, etc.); (3) history of epilepsy (hyperpyretic convulsion in the childhood excepted); (4) alcohol or drug dependence in the previous year; (5) anxiety resulting from other mental or physical disorders; (6) pregnant or breastfeeding women or women who plan to conceive during the study period; (7) history of severe drug allergy or allergy to buspirone; (8) participation in other clinical drug trials in the previous 30 days; (9) intake of monoamine oxidase inhibitor or buspirone in the previous 4 weeks; (10) regular medicine intake cannot be guaranteed because of being uncared or other reasons; (11) a reduction of the HAM-A score of at least 25% at baseline compared with the screening time; and (12) a Hamilton Depression Rating Scale-17 (HAMD-17) score of more than 7 at screening.

### Randomization and allocation concealment

Eligible participants will be randomly assigned to either the study group or the control group in a ratio of 1:1. A computer-generated random allocation sequence will be produced by an independent statistician using SAS software (SAS Institute, Cary, NC, USA). Based on the allocation sequence, drug packages will be labeled serially. Participants will receive the corresponding drug package in the order of recruitment. The complete random sequence will be kept by the primary researcher in Beijing Anding Hospital. Emergency envelopes containing the random allocation individually will be prepared for each center, which can be unsealed only in the case of serious adverse events.

### Blinding

Pharmacists in charge of labeling the drug packages do not take part in the conduction of the trial. Participants and researchers responsible for screening, recruitment, dispensing medicine, and outcome assessment will all be blind to the group allocation. Statistical analysis will be conducted by independent statisticians who will know only the group codes but not the corresponding interventions.

### Interventions

Participants allocated to the study group will receive SGQR formula and buspirone placebo, while buspirone and SGQR placebo will be applied in the control group. The drug and its matching placebo will have a similar appearance, weight, and taste. SGQR formula and placebos will be provided by Tiansheng Taifeng Pharm Co. Ltd. (Lhasa, Tibet, China), and buspirone will be manufactured by Enhua Pharm Co. Ltd. (Xuzhou, Jiangsu, China).

SGQR formula is prepared in the form of condensed pills. The pills will be packed at a unit of 4 grams, whose ingredient is equivalent to Radix Paeoniae Alba 1.14 g, Radix Bupleuri 0.86 g, Angelica Sinensis 0.57 g, Radix Curcumae 0.57 g, Poria Cocos 0.69 g, Bulbus Lilii 0.69 g, Cortex Albiziae 0.69 g, Radix Glycyrrhizae 0.34 g, *Triticum aestivum* L 0.86 g, and Fructus Jujubae 0.57 g, 10 herbals in total.

There will be three dosages of drugs: the starting dosage (SGQR formula or placebo 4 g t.i.d., combined with buspirone or its placebo 5 mg b.i.d.), the low dosage (SGQR formula or placebo 4 g t.i.d., combined with buspirone or its placebo 5 mg t.i.d.), and the high dosage (SGQR formula or placebo 8 g t.i.d., combined with buspirone or its placebo 10 mg t.i.d.).

In the first week of intervention, participants will be prescribed the starting dosage for the first three days and the low dosage for the remaining four days. From the second week on, the dosage will be adjusted by the researchers. The recommended indicator for doubling to high dosage is a reduction of not more than 25% of the HAM-A score compared with the baseline after the first week’s intervention, keeping low dosage otherwise. Moreover, high dosage and low dosage can be alternated anytime during the intervention period in accordance with patient’s reaction to the previous treatment.

Drugs and placebos covering the whole course of treatment for each participant will be packed uniformly and individually. In each center, there will be a pharmacist responsible for dispensing the prescription. At every visit, participants will receive the drugs scheduled for the next intervention period, and the drugs left from the previous period will be returned. The dosage will be explained to the participants orally and in writing and also recorded in a medical booklet. Medication compliance will be calculated accordingly. The scheduled duration of treatment is 8 weeks unless a serious adverse event happens or the participant quits. Non-pharmacologic care is permitted but other psychiatric medication is prohibited. Administration and dosage of concomitant medication for physical conditions will be permitted and recorded in detail.

Any question raised by the participants will be answered to promote completion. The detailed study schedule is listed in Fig. 2.

**Fig. 2 Fig2:**
[figure not shown]
Study schedule

### Outcome measurements

Outcome measurements are scheduled at screening, baseline, and the end of weeks 1, 2, 4, and 8.

#### Basic characteristic variables

Basic data of all the participants, including name, gender, date of birth, marital status, educational level, date of diagnosis, and medical history, will be collected. General physical examination results, including vital signs (body temperature, blood pressure, respiratory rate, and heart rate), will also be recorded. Concomitant medication will be inquired about and documented at every visit.

#### Primary outcome

HAM-A, which is one of the first and most widely used rating scales to measure the severity of anxiety symptoms, will be set as the primary outcome [7]. There are 14 items in the HAM-A, which incorporate groups of symptoms (such as fears, autonomic symptoms, and respiratory symptoms) rather than specific, single symptoms. Each item is rated from 0 to 4; the higher the score, the worse the situation. The good reliability and validity of HAM-A make it a standard interviewer-administered instrument [8].

#### Secondary outcomes

HAMD-17 is set as one of the secondary outcomes because comorbidity of depression and anxiety is rather common in health-care settings [9]. HAMD-17, a multi-dimensional rating scale that covers a range of clinical features associated with depression, is the standard efficacy outcome for depression severity evaluation, treatment response, and remission measurement [10, 11]. The higher the HAMD-17 score, the worse the situation.

Another secondary outcome focuses on the improvement in overall symptom severity and functioning, measured by using the Clinical Global Impression-Improvement Scale (CGI-I), which consists of a 7-point global rating (1 = very much improved, 4 = no change, and 7 = very much worse) [12]. This scale has also been widely used in clinical studies on GAD.

The TCM Syndrome Scale for GAD is a tailored scale for GAD and is based on the theory of TCM. It concentrates more on subjective discomfort in combination with objective clinical signs. Subjective discomfort includes worry without reason, hesitation, being easily frightened, and a disinclination to talk because of a deficiency of qi. These symptoms may not be fatal but always trouble the patient seriously. Objective clinical signs focus on the complexion, color of the lips and tongue, tongue coating, and the pulse. When the patient is evaluated with this scale, the differentiation and severity of the TCM syndrome can be concluded.

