### Sample size calculation

As there is no large randomized controlled trial of SGQR formula for GAD, we referred to the experience of experts in this field. A response rate of 91% for SGQR was assumed. As to buspirone, the response rate was about 75%, according to the literature [16]. In the setting of α = 0.05 and β = 0.2, the sample size was calculated to be 83 in each group. Given a 20% dropout rate, 17 more participants will be required in each group. In total, 200 participants will be enrolled.

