### Data management and analysis

CRFs will be entered by two independent researchers and supervised by a third one to ensure accuracy. Data analysis will be performed by statisticians who are blind to the randomization by using SPSS (Statistical Product and Service Solutions) Statistics for Windows, version 20.0 (IBM Corp., Armonk, NY, USA). Continuous variables will be presented as mean and standard deviation, and categorical variables will be presented as frequency or percentage. Demographic data and outcome measurements at baseline will be listed to ensure relatively even baseline levels. A *t* test (if normally distributed) or non-parametric test (if not normally distributed) will be used for continuous variables when conducting baseline comparisons. The repeated measures ANOVA (analysis of variance) will be used when analyzing the primary and secondary outcomes. Chi-squared or non-parametric test will be applied for categorical variables. The analysis of efficacy will be performed in accordance with the intention-to-treat principle. Missing values will be imputed by the last observation carried forward method. Subgroup analysis will be conducted if necessary. A *P* value of less than 0.05 will be considered statistically significant. A mixed-effects model for repeated measures will be performed as a sensitivity analysis of the primary efficacy outcome.

Mid-term date analysis will be conducted after half of the recruitment is finished, and the principal investigator will decide whether any measure should be taken in light of the results. All of the data will be deposited in the platform developed by our team. Anding Hospital will be responsible for the data, and other researchers can have access to the data only after application and permission.

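### HAMD-17 is a secondary outcome because comorbid depression is common, but the entry criteria exclude patients scoring above 7, so the result cannot speak to benefit on comorbid depression

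*Protocol article*

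**What the plan says.** In the protocol article, Secondary outcomes gives the reason for the scale: "HAMD-17 is set as one of the secondary outcomes because comorbidity of depression and anxiety is rather common in health-care settings". It adds that HAMD-17 "is the standard efficacy outcome for depression severity evaluation, treatment response, and remission measurement", and that "The higher the HAMD-17 score, the worse the situation".

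Exclusion criterion 12 removes any patient with "a Hamilton Depression Rating Scale-17 (HAMD-17) score of more than 7 at screening". Criterion 5 also removes patients with "anxiety resulting from other mental or physical disorders".

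Data management and analysis gives HAMD-17 the same method as HAM-A: "The repeated measures ANOVA (analysis of variance) will be used when analyzing the primary and secondary outcomes".

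The article states no other role for HAMD-17, such as watching for depression that emerges on treatment. It is not listed under Safety outcomes.

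**The concern.** The outcome is justified by a comorbidity that the entry criteria largely screen out. Patients admitted with a HAMD-17 score of 7 or less have little depression that could respond or remit, yet those are the uses for which the article presents the scale.

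Two misreadings are at stake. A non-significant result could be reported as the two drugs having the same effect on depression, when the entry rule left little to reduce. A significant result could be reported as an added benefit in anxious patients with depression, a group that was not enrolled. The data support neither statement.

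**Working it through.** **1. The sections side by side.**

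| Scale | Role | Entry limit | Room to improve |
|---|---|---|---|
| HAM-A | primary | "Hamilton Anxiety Rating Scale (HAM-A) scores between 14 and 39 (inclusive) at screening and baseline" | minimum of 14 ensures it |
| HAMD-17 | secondary | above 7 at screening excluded | upper limit only, no minimum |

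Everyone enrolled scores 7 or less on HAMD-17 at screening. If the scale starts at 0 (an assumption, since the article gives no range), the largest possible fall from the screening score is 7 − 0 = 7 points. The limit is not repeated at baseline, so a baseline score can exceed 7.

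**2. The trial's own sample size.** It rests on response rates of 91% and 75%, not on HAMD-17. With two-sided α = 0.05 (sidedness assumed), power 80% and unpooled variance:

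n = (1.96 + 0.84)² × (0.91 × 0.09 + 0.75 × 0.25) / (0.91 − 0.75)² = 82.6, so 83 per arm.

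This reproduces the stated 83. The plan adds 17, giving 100 per arm, or 80 completers at 20% dropout. These numbers are used below. The article gives no HAMD-17 means or SDs, so every such value below is an assumption.

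**3. What mean difference could be detected.** Detectable difference at 80% power = SD × √(2/n) × (1.96 + 0.84).

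| Assumed SD | 100 per arm | 80 per arm |
|---|---|---|
| 1.5 | 0.59 | 0.66 |
| 2 | 0.79 | 0.89 |
| 3 | 1.19 | 1.33 |

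Power for a 1-point difference at 100 per arm is 0.997, 0.94 and 0.65 for SD 1.5, 2 and 3. A shift of about one point can therefore reach significance.

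**4. How large a difference to expect.** Suppose one arm's scores fall by 60% and the other's by 40%.
- After the cut, with an assumed baseline mean of 3 to 6: 0.20 × 3 = 0.6 to 0.20 × 6 = 1.2 points.
- Without the cut, with an assumed mean of 8 to 12: 0.20 × 8 = 1.6 to 0.20 × 12 = 2.4 points.

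**5. Power on a like-for-like basis.** Simulated two-sample t test, 80 per arm, 60% against 40% reduction, floor at 0, residual SD 2.5, same source population with and without the cut:

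| Source population | With cut at 7 | Without cut |
|---|---|---|
| mean 8, SD 4 | about 58% to 61% | about 90% to 92% |
| mean 12, SD 4 | about 74% to 75% | over 99% |

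For the first source with the cut, power is about 78% at residual SD 2 and 47% at residual SD 3. Sensitivity is reduced but not lost.

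**The case against.** The strongest reply is that the outcome still measures something. A reader might infer that patients sit at the floor of the scale, that improvement is capped at 7 points, and that the trial can show no HAMD-17 effect at all. The documents do not support that reading. The limit applies at screening only, whereas HAM-A is checked at screening and baseline, so change from baseline has no 7-point cap. Scores of 0 to 7 are the bottom range of the scale, not zero. A difference of about one point is detectable, and power of 58% to 75% is not unusual for a secondary outcome on which the trial was not sized. This part of the reply stands.

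It is also fair that the sentence on severity, response and remission describes the instrument in general. The article defines no HAMD-17 response or remission endpoint and announces no claim about treating comorbid depression. A comparison of means would register worsening as well as improvement, and adverse symptoms are checked separately with TESS at every visit. Excluding patients with higher depression scores may be a sensible way to enrol relatively pure GAD.

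These points limit the consequence but leave the conflict. The only reason printed for the outcome is comorbid depression, and the entry rule screens it out. A separate analysis plan could add detail to the HAMD-17 analysis, but it would not make the two printed statements agree.

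**Conclusion.** The point holds as a mismatch between the stated purpose of HAMD-17 and the enrolled population. The trial can detect small shifts in low-level depressive symptoms, or worsening. It cannot inform on severity, response or remission of comorbid depression, whichever way the result falls.

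The conflict follows from the text alone. Its size rests on the assumed HAMD-17 minimum, means and SDs: an expected difference of roughly 0.6 to 1.2 points instead of 1.6 to 2.4, and power of about 58% to 75% instead of 90% to over 99% at residual SD 2.5. The consequence is confined to one secondary outcome and what may be claimed from it. The HAM-A primary outcome and the sample size are not affected. It is worth correcting because the remedy is almost free and changes what the report may say.

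**What to change.** Reconcile Secondary outcomes with exclusion criterion 12, leaving the criterion as it is:

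- Restate HAMD-17 as a measure of low-level or emerging depressive symptoms in patients without notable depression at screening.
- Keep the planned between-arm comparison of scores, preferably adjusted for baseline HAMD-17, and report the difference with its 95% CI.
- State that no conclusion will be drawn on treating comorbid depression, nor on equal antidepressant effect of the two drugs.

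One tempting alternative should not become the main analysis: counting patients who score above 7 at any visit after baseline. That line coincides with the screening cut, so crossings would largely reflect regression to the mean and measurement error. In a simulation with no true change (source mean 8 to 10, SD 4, assumed visit-to-visit error SD 1.5 to 2.5), 38% to 77% of patients cross it at one of the four visits at weeks 1, 2, 4 and 8. Between 19% and 44% already exceed 7 at baseline. Even among those at 7 or less at baseline, 27% to 65% cross.

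The cost is wording, plus the written application to the ethics committee that the article requires for protocol changes. No visits, patients or data are added. The trial gives up an efficacy claim on depression that its entry criteria already rule out. The change is best made before unblinding.
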